**Methods:**

This prospective cohort study aims to investigate differences in mRNA expression of the abovementioned proteins between the ventral and dorsal tunica dartos in patients with hypospadias and chordee. Ethics approval has been obtained, and consent from parents will be obtained before data collection. Eligible participants are aged 6-18 months, diagnosed with hypospadias and chordee, and planned for urethroplasty. Tissue samples will be collected from both aspects of the tunica dartos and analyzed using real-time quantitative reverse transcription–polymerase chain reaction. Data analysis will involve statistical tests and normalization of housekeeping genes.

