### Clinical Outcomes

The clinical outcomes measured in this study are as follows:

Expression of fibulin-1 mRNAExpression of elastin mRNAExpression of MMP-1 mRNAExpression of bFGF mRNAExpression of α-SMA mRNA

The clinical outcomes will be measured from differences in mRNA expression from both the dorsal and ventral aspects of the tunica dartos excised during urethroplasty. A positive control gene for both dorsal and ventral tissues will also be measured in subsequent analyses. The expression levels of the 5 genes will be assessed relative to the housekeeping gene β-actin using fold change values.

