### Study Process and Data Collection

#### Specimen Collection

In this study, tissue samples from the dorsal and ventral sides of the tunica dartos will be obtained from patients with hypospadias and chordee. Ventral tunica dartos samples will be taken from each patient by the researcher as the performing operator, ensuring that the size and location of collection are standardized across all patients. The collected portions are shown in Figure 1.

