### Data Analysis

The data to be collected in this study include clinical characteristics such as age, height, weight, BMI, comorbidities, and delivery history, accompanied by mRNA expression from both the dorsal and ventral sides of the tunica dartos tissue.

All quantitative data obtained from this research will be analyzed using SPSS (version 25.0; IBM Corp) software. The normality of all numeric data will be tested using the Kolmogorov-Smirnov test. Numeric data will be presented as mean (SD) for normally distributed data and median (range) for nonnormally distributed data.

If the obtained data are normally distributed, an independent 2-tailed *t* test will be performed. Meanwhile, nonnormally distributed data will be tested using the Mann-Whitney *U* test to determine gene expression differences between research groups. The quantification of gene expression is expressed as fold change, compared to the housekeeping gene used in the study.

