Notable distinctions in collagen and elastin content are observed between normal and hypospadias-afflicted penises, affecting the stiffness and flexibility of the tunica dartos [7]. There are some proteins that play roles in the elasticity of a tissue. Elastic connective tissue is pivotal in various pathological tissue changes. Elastin, an essential component of the extracellular matrix, endows tissues with extensibility and elasticity. Low elastin concentrations are linked to impaired male urethral development, while elastin-rich concentrations in male fetus urethras elevate intrauterine pressure during the early stages of micturition [14]. Matrix metalloproteinases play a key role in embryological processes and wound healing. MMP-1, a collagenase enzyme, breaks down collagen types I, II, and III, influencing extracellular matrix repair. Decreased MMP-1 levels in hypospadias are linked to increased collagen production. Unbalanced collagen synthesis and degradation can lead to fibrotic tissue formation [15]. Fibroblast growth factors regulate fibroblast growth and differentiation. bFGF stimulates cell proliferation and differentiation, impacting the mesodermal, ectodermal, and endodermal areas. Abnormalities in the bFGF pathway contribute to urethral plate formation, potentially resulting in fibrotic tissue development. α-SMA, implicated in fibrogenesis, drives myofibroblast differentiation and extracellular matrix repair. In the context of hypospadias, α-SMA involvement points to fibrocontractive diseases such as chordee [16].

While this study may provide insights into the differences of the ventral and dorsal tunica dartos, we did not include samples of tunica dartos from healthy patients, which would limit the data analysis only to patients with chordee.

Understanding the differential mRNA expression of fibulin-1, elastin, MMP-1, bFGF, and α-SMA between the ventral and dorsal tunica dartos in patients with hypospadias and chordee presents an opportunity to explore the intricate molecular mechanisms underlying hypospadias development and its associated complications.

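### Ventral and dorsal tissue come from the same child, but the plan compares them with tests for unrelated groups, so the p-values are wrong and much of the power can be lost

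*Protocol article*

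**What the plan says.** The article describes one cohort sampled at two sites:

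- Abstract, Methods: "Tissue samples will be collected from both aspects of the tunica dartos".
- Clinical Outcomes: the outcomes are "differences in mRNA expression from both the dorsal and ventral aspects of the tunica dartos excised during urethroplasty".
- Specimen Collection: "tissue samples from the dorsal and ventral sides of the tunica dartos will be obtained from patients with hypospadias and chordee", and "Ventral tunica dartos samples will be taken from each patient by the researcher as the performing operator".
- Data Analysis (last part of Methods): each patient's clinical characteristics are recorded, "accompanied by mRNA expression from both the dorsal and ventral sides of the tunica dartos tissue".
- Discussion, on limitations: "we did not include samples of tunica dartos from healthy patients".

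The same Data Analysis section then fixes the tests. For normal data: "If the obtained data are normally distributed, an independent 2-tailed" t test. Otherwise: "Meanwhile, nonnormally distributed data will be tested using the Mann-Whitney" U test. It describes the comparison as one between research groups. The article mentions no paired t test, signed-rank test or mixed model.

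**The concern.** The only two groups that can be compared are the two sides of the same children. Both named tests treat the ventral and dorsal values as coming from unrelated children. Differences between children that affect both sides alike, such as age, genotype or severity, then stay in the error term, although they cancel in a within-child difference.

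This is the only inferential analysis of the study's only aim. With positive correlation, the error pushes towards a non-significant result. The Discussion reports that earlier studies saw no ventral-dorsal difference and links the matter to a surgical debate about excising ventral dartos. A false null would therefore look like replication.

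**Working it through.** **Inputs from the article.** Two sites per child in one cohort; two-tailed t test for independent samples, or Mann-Whitney U. It states no sample size, alpha, effect size, SD or ventral-dorsal correlation, so there is no figure of the plan's own to reproduce.

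**Assumptions.** n = 20 children, two-sided alpha 0.05, normal data with equal SD σ on both sides, and within-child correlation ρ from -0.3 to 0.7. The effect d is the mean ventral-dorsal difference divided by σ.

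**Step 1: standard error.** The true variance of the mean difference is 2σ²(1-ρ)/n. The independent test uses 2σ²/n. The standard error is therefore misstated by a factor 1/√(1-ρ):

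- ρ = 0.3: 1/√0.7 = 1.20
- ρ = 0.5: 1/√0.5 = 1.41
- ρ = 0.7: 1/√0.3 = 1.83
- ρ = -0.3: 1/√1.3 = 0.88

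**Step 2: type I error.** The large-sample formula is 2[1-Φ(1.96/√(1-ρ))]. It gives 1.9%, 0.56% and 0.03% at ρ = 0.3, 0.5 and 0.7, and 8.6% at ρ = -0.3. The table gives simulated values for n = 20.

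**Step 3: power.** The effect is set so that the paired t test has 80% power: d = 1.06, 0.93, 0.78, 0.66 and 0.51 down the rows. A second comparison fixes d = 0.5.

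| ρ | Type I error, independent t | Type I error, Mann-Whitney | Independent t where paired t has 80% power | d = 0.5: independent v paired |
|---|---|---|---|---|
| -0.3 | 8.4% | 8.4% | 88% | 36% v 26% |
| 0 | 5.0% | 4.9% | 82% | 34% v 32% |
| 0.3 | 2.1% | 2.0% | 70% | 31% v 43% |
| 0.5 | 0.7% | 0.8% | 54% | 28% v 56% |
| 0.7 | 0.1% | 0.1% | 27% | 25% v 78% |

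The t test columns use 200,000 replicates and the Mann-Whitney column 10,000. The paired t test held its type I error at about 5% in every row. Runs with 10 and 30 children show the same pattern.

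**Step 4: children needed for 80% power at d = 0.5 (normal approximation).**

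- Paired test: 2(1-ρ)[(1.96+0.842)/0.5]² = 62.8(1-ρ), so 44, 32 and 19 children at ρ = 0.3, 0.5 and 0.7.
- Planned test on the same paired data: 2[(1.96+0.842√(1-ρ))/0.5]², so 57, 53 and 47 children.
- The ratios are 57/44 = 1.3, 53/32 = 1.7 and 47/19 = 2.5.

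**The case against.** **Is the pairing certain?** Specimen Collection says that a sample is taken from each patient only for ventral tissue, and the number of specimens per side is not given. Pairing is thus partly an inference. But no second set of children is described, healthy controls are ruled out, and both sides are listed among the data to be collected. No other reading is sensible.

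**Is the loss overstated?** This objection largely stands. More than half of the power is lost only from a correlation of about 0.6 to 0.7. At 0.3 the loss is about 10 points and at 0.5 about 26. The correlation is unknown. RNA yield and tissue quality vary largely by specimen and do not cancel in a within-child difference. Dilution to a common concentration, β-actin normalization and the narrow age range may also reduce the variation that a child's two sides share. The higher correlations are therefore unproven.

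**Are false positives a risk?** Only if the correlation is negative. Nothing in the article supports that, and the common origin of the two tissues noted in the Discussion points the other way.

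**Could a separate analysis plan settle it?** A published article may leave detail to another document, but this one names the tests. A later plan could correct them only by contradicting it.

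**Does the ΔΔCt method already pair the data?** If each child's dorsal sample were the calibrator, there would be one value per child and nothing for a two-group test to compare. The Data Analysis section instead expresses fold change relative to the housekeeping gene and compares groups.

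**Conclusion.** The concern holds. Both tests named for the study's only comparison assume independence that the design does not provide. Their p-values are valid only if the within-child correlation is zero, which is implausible for two specimens from one child at one operation.

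That error follows from the text alone. Its size depends on assumptions: 20 children, normal data, two-sided 5% level and correlations of 0.3 to 0.7. Under these, power falls from 80% to between 70% and 27%, and the nominal 5% test operates at between 2.1% and 0.1%. The likely consequence is a missed difference. It must be corrected before the analysis is run.

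**What to change.** Replace the two test sentences in Data Analysis with wording such as:

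*For each gene, the within-child difference d = ΔCt(ventral) - ΔCt(dorsal) will be tested against zero with a two-sided paired t test, or with the Wilcoxon signed-rank test if the differences are clearly non-normal. Normality will be assessed on the differences. Children with both specimens will be analysed.*

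The essential change is the paired test with the normality check moved to the differences. Naming the paired t test as primary with signed-rank as a sensitivity analysis would also be acceptable. Working on the ΔCt scale and giving the mean difference with its 95% confidence interval are advisable additions.

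State also that a study code links each child's two specimens after de-identification. The Ethical Considerations section says identifiers are removed before analysis but does not mention this link, and without it the pairing could not be recovered.

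The cost is a few sentences, with no extra patients or assays. SPSS, the software already named, can run both tests.

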## Results

This study is at the protocol development stage. A pilot study regarding its feasibility has been ongoing as of August 2023. The study results are expected to be available by the end of 2024.

## Discussion

Hypospadias, characterized by the abnormal positioning of the urethral opening, is a prevalent condition that ranks as the second most frequent congenital anomaly in male neonates, following cryptorchidism. The condition is typified by the displacement of the urethral meatus to the ventral side of the penis, leading to curvature abnormalities in the penis and preputial skin. The quest for optimal restoration, both functionally and aesthetically, drives the need for hypospadias correction surgeries. The primary aim of these interventions is to achieve acceptability in both the appearance and function of the penis, while also addressing psychological concerns [1,2].

The realm of hypospadias surgery presents a diversity of approaches for penile reconstruction, yet controversies persist regarding the most suitable techniques for various types of hypospadias and the utilization or excision of tunica dartos in surgical procedures. Noteworthy among these techniques is the “tubularized incised plate” urethroplasty proposed by Snodgrass et al [11], utilizing tunica dartos excision to address chordee. Another technique, similar in approach but employing tunica dartos or tunica vaginalis as a second layer, was presented by Tavakkoli Tabassi and Mohammadi [12]. Diverging opinions among urologists surround the excision of all inelastic tissue (ventral tunica dartos), coupled with dorsal tunica dartos as a second layer. Intriguingly, prior studies failed to find disparities between the ventral and dorsal tunica dartos, attributing this to their concurrent formation and common origin [4,7,13].

The multifactorial etiology of hypospadias is underscored by its potential maternal and paternal inheritance, suggesting a likelihood of 57% to 77% heritability. Environmental factors, including exposure to chemicals, such as pesticides, diethylstilbestrol, vinclozolin, polychlorinated biphenyls, phthalates, and dioxins during pregnancy, have been implicated in hypospadias causation [3,4]. While the exact etiology of hypospadias remains elusive, histopathological findings in patients with hypospadias warrant further investigation into the disorder’s etiological landscape [7].

Notable distinctions in collagen and elastin content are observed between normal and hypospadias-afflicted penises, affecting the stiffness and flexibility of the tunica dartos [7]. There are some proteins that play roles in the elasticity of a tissue. Elastic connective tissue is pivotal in various pathological tissue changes. Elastin, an essential component of the extracellular matrix, endows tissues with extensibility and elasticity. Low elastin concentrations are linked to impaired male urethral development, while elastin-rich concentrations in male fetus urethras elevate intrauterine pressure during the early stages of micturition [14]. Matrix metalloproteinases play a key role in embryological processes and wound healing. MMP-1, a collagenase enzyme, breaks down collagen types I, II, and III, influencing extracellular matrix repair. Decreased MMP-1 levels in hypospadias are linked to increased collagen production. Unbalanced collagen synthesis and degradation can lead to fibrotic tissue formation [15]. Fibroblast growth factors regulate fibroblast growth and differentiation. bFGF stimulates cell proliferation and differentiation, impacting the mesodermal, ectodermal, and endodermal areas. Abnormalities in the bFGF pathway contribute to urethral plate formation, potentially resulting in fibrotic tissue development. α-SMA, implicated in fibrogenesis, drives myofibroblast differentiation and extracellular matrix repair. In the context of hypospadias, α-SMA involvement points to fibrocontractive diseases such as chordee [16].

While this study may provide insights into the differences of the ventral and dorsal tunica dartos, we did not include samples of tunica dartos from healthy patients, which would limit the data analysis only to patients with chordee.

Understanding the differential mRNA expression of fibulin-1, elastin, MMP-1, bFGF, and α-SMA between the ventral and dorsal tunica dartos in patients with hypospadias and chordee presents an opportunity to explore the intricate molecular mechanisms underlying hypospadias development and its associated complications.

## Abbreviations

α-SMA: α-smooth muscle actin
bFGF: basic fibroblast growth factor
Ct: cycle threshold
MMP-1: matrix metalloproteinase-1
mRNA: messenger RNA
qRT-PCR: real-time quantitative reverse transcription–polymerase chain reaction
SPIRIT: Standard Protocol Items: Recommendations for Interventional Trials
